### Trial status

The trial is currently being set up with participant recruitment. Recruitment will cease when 114 participants have been randomized; it is expected this target will be reached by June 2017.

## Discussion

This is a multicenter study designed to ascertain if a supervised multicomponent exercise program carried out in long-term nursing care centers improves or maintains functionality, sedentary behaviors, cognitive and emotional status and biological markers related to frailty when compared with a control population that receives usual care. To our knowledge, an exercise program carried out in nursing home elderly population has not been studied before from a so broad perspective, taking into account all together functional, cognitive, emotional and biochemical conditions. The current lack of definitive evidence on whether ageing related functional deterioration can be effectively prevented by physical exercise in institutionalized elders represents a potential obstacle to the development of guidelines for geriatric clinicians and policymakers that would also report in increasing health-related quality of life for a prevalent and clinically-relevant population. Furthermore, the World Health Organization (WHO) has recently published an Action Plan for the Prevention and Control of Noncommunicable Diseases in the WHO European Region 2016–2025, where it is highlighted the importance of introducing systematic musculoskeletal health programs for older people, including those living in residential care [82]. Moreover, long-term nursing home residents have been identified as a particularly vulnerable group where the above mentioned plan should direct its actions through an early intervention to restore and maintain functionality.

The exercise program that is described in this protocol has been designed to be feasible, easy to implement and potentially delivered in any nursing home settings, which may have direct clinical applications. We previous reported [83] that a similar multicomponent exercise program is feasible, well tolerated and pleasantly welcomed by individuals living in long-term care facilities. Furthermore, improvements in functional status were observed in those participants that took part in the program, particularly in gait ability, balance and aerobic capacity. These findings are in line with other studies carried out in nursing homes, indicating that the exercise programs can benefit functional performance, well being and cognition of the residents [84–88]. Nevertheless, to date few randomized clinical trials have been conducted in institutionalized elders, and normally these trials study heterogeneous interventions (sometimes poorly explained), while our study allows the extrapolation of results and the implementation of the program to any other nursing home through a well-defined methodology.

Finally, if the described multicomponent exercise program proves to report benefits in terms of functional, sedentary behavior, cognitive and emotional status, as well as knowledge on the response of biological markers to physical activity, the findings could provide evidence suggesting the need to augment the standard physical practice prescribed at nursing homes in the elder population. Otherwise, failure to reject the null hypothesis would suggest that the progression of the decline associated with the aging process in at-risk persons continues on to disability, despite any potential benefits from physical activity. This would be an important study outcome as well and implies that efforts to hold back the process of disablement in this population should be directed elsewhere.

The study of whether multicomponent exercise program can improve or maintain functionality, sedentary behaviors, cognitive and emotional status and biological markers related with frailty in nursing home elders is nowadays an unanswered question that is of major importance to public health and social policy. It is expected that the results of this research will guide clinical practice in nursing home settings, so that clinicians and policymakers can provide more evidence-based practice for the management of institutionalized elder people.

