**Methods:**

This is a multicentre randomized controlled trial. 114 participants will be randomly allocated to a usual care group or to an intervention group. Inclusion criteria are as follows: ≥ 70 years, ≥ 50 on the Barthel Index, ≥ 20 on MEC-35 who are capable to stand up and walk independently for 10 m. Subjects in the intervention group will add to the activities scheduled for the control group the participation in a 6 months long multicomponent exercise program designed to improve strength, balance and walking retraining. Study assessments will be conducted at baseline and at 3 and 6 months. The primary outcome is change in function assessed by Short Physical Performance Battery and secondary outcomes include other measurements to assess all together the condition of frailty, which includes functionality, sedentary behaviors, cognitive and emotional status and biological markers. The present study has been approved by the Committee on Ethics in Research of the University of the Basque Country (Humans Committee Code M10/2016/105; Biological Samples Committee Code M30/2016/106).

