**Discussion:**

Results from this research will show if ageing related functional and cognitive deterioration can be effectively prevented by physical exercise in institutionalized elders. It is expected that the results of this research will guide clinical practice in nursing home settings, so that clinicians and policymakers can provide more evidence-based practice for the management of institutionalized elder people.

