## Objective

To the knowledge of the authors, no studies have explored the effects of a supervised multicomponent exercise program carried out in long-term nursing care centers from a broad perspective of the condition of frailty, assessing all together functionality, sedentary behaviors, cognitive and emotional status and biological markers. Thus, it has been designed a randomized multicenter study to test the hypothesis that the addition of a multicomponent exercise program to the usual care in institutionalized elders can improve their functionality in 1 point in the Short Physical Performance Battery (SPPB).

The major aim of this study is to ascertain if a supervised multicomponent exercise program carried out in long-term nursing care centers improves or maintains functionality, sedentary behaviors, cognitive and emotional status, health related quality of life and modifies biological markers related to frailty when compared with a control population that received usual care.

The present study is based on a previous pilot study [50] in which we successfully collected preliminary data to accurately demonstrate the feasibility of recruitment, estimate the required sample size for the current trial, confirm the adherence and safety of the intervention, refine the outcome assessments, and optimize the organizational infrastructure.

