### Statistical considerations

The IBM SPSS Statistics 23 statistical software package (SPSS, Inc., Chicago, IL) will be used to analyse the data. Intention to treat analyses will be performed. The normal distribution of the data will be evaluated using the Kolmogorov-Smirnov test. Continuous variables will be expressed as mean (SD) when normally distributed and as median with interquartile range (IQR) when not. Categorical variables will be expressed as frequency counts and percentages. Statistical comparisons at baseline will be performed using appropriate statistical tests according to the type and distribution of the data: *t* test or Mann–Whitney *U*-test for continuous variables and Chi-squared test for categorical variables. The intervention-related effects will be performed using appropriate statistical tests according to the type and distribution of the data: an analysis of variance (ANOVA) or Friedman test with repeated measures (0, 3 and 6 months). When a significant F value is obtained, LSD post hoc procedures will be used to evaluate pairwise differences. *p* < 0.05 will be considered to be statistically significant. Furthermore, an analysis of covariance (ANCOVA) will be done to compare the data between intervention and control groups, considering as co-variables baseline measurements, as well as other variables as age or gender.

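### The major aim and the abstract put secondary domains, notably cognition, on equal terms with the SPPB, and one p < 0.05 rule covers every test, so an isolated secondary positive cannot carry a domain claim at the nominal 5% level.

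*Protocol article*

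**What the plan says.** The protocol article ranks one outcome above the rest. The abstract's Methods states: "The primary outcome is change in function assessed by Short Physical Performance Battery and secondary outcomes include other measurements". The Objective section gives a single hypothesis, that adding the programme to usual care "can improve their functionality in 1 point in the Short Physical Performance Battery (SPPB"). Power and sample size uses the SPPB alone.

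Other passages do not keep to that ranking:

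- **Objective, major aim.** The trial is to find out whether the programme "improves or maintains functionality, sedentary behaviors, cognitive and emotional status, health related quality of life and modifies biological markers related to frailty". Function and five other domains stand side by side.
- **Abstract, Discussion.** "Results from this research will show if ageing related functional and cognitive deterioration can be effectively prevented by physical exercise in institutionalized elders". Only the cognitive tests, all secondary, can answer the cognitive half of that sentence.
- **Statistical considerations.** A single rule is given, p "< 0.05 will be considered to be statistically significant", with no distinction between primary and secondary tests. After a significant F value, "LSD post hoc procedures will be used to evaluate pairwise differences"; in addition, "an analysis of covariance (ANCOVA) will be done to compare the data between intervention and control groups".
- **Discussion, main text.** A possible change to standard practice in nursing homes is considered "if the described multicomponent exercise program proves to report benefits in terms of functional, sedentary behavior, cognitive and emotional status".

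**The concern.** The document makes two kinds of statement that do not fit together. Its labels say that one outcome is confirmatory. Its aim and the abstract's conclusion say that the trial will also settle questions in domains that only secondary measures address. The one significance rule treats all of these tests alike.

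A 5% threshold limits the error of one test. Where a domain claim may draw on any of several tests, the chance that at least one is positive by luck is larger. A report that follows the article as written could present a single cognitive, emotional, quality-of-life or biomarker result at p < 0.05 as an answer to the major aim. At stake is how far readers may trust such a claim, since the article expects the trial's results to guide clinicians and policymakers. The primary SPPB comparison is not at issue.

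**Working it through.** **The plan's own figure.** The article states a per-test threshold of 0.05 and no familywise error rate, so there is no stated familywise figure to reproduce.

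**Step 1: count the secondary measures (Outcome measures, Tables 3 to 5).**

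| Domain | Measures | Number |
|---|---|---|
| Function, besides SPPB | Senior Fitness Test, instrumented Timed Up and Go, walking speed, handgrip, Berg, stabilometry | 6 |
| Sedentary behaviour | accelerometry | 1 |
| Cognition | CDR, MoCA, SDMT | 3 |
| Emotional status | Goldberg scale | 1 |
| Quality of life | EQ-5D-5L | 1 |
| Biomarkers | myostatin, irisin, IL-6, BDNF | 4 |

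The total is 6 + 1 + 3 + 1 + 1 + 4 = 16. The five further domains hold 1 + 3 + 1 + 1 + 4 = 10. Falls, emergency visits, hospital admissions and length of stay would add 4 more and are left out.

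**Step 2: independent tests, no true effect, one two-sided 5% between-group test per measure at one visit.** The chance of at least one p < 0.05 among k tests is 1 − 0.95^k.

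- k = 16: 1 − 0.440 = 0.56
- k = 10: 1 − 0.599 = 0.40

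The expected number of false positives among the 16 is 16 × 0.05 = 0.8, whatever the correlation.

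**Step 3: correlated tests.** The article gives no correlations between outcomes, so these are assumptions. With a common correlation r between the test statistics, Φ the normal distribution function and φ its density,

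P = 1 − ∫ [Φ((1.96 − √r·u)/√(1−r)) − Φ((−1.96 − √r·u)/√(1−r))]^k φ(u) du.

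| Tests | r = 0 | r = 0.5 | r = 0.8 |
|---|---|---|---|
| 16, either direction | 0.56 | 0.37 | 0.21 |
| 10, either direction | 0.40 | 0.29 | 0.17 |
| 16, favouring exercise only | 0.33 | 0.19 | 0.10 |

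The last row uses only the upper 2.5% tail; at r = 0 it is 1 − 0.975^16 = 0.33. The matching rate for one test is 0.025.

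**Step 4: a more realistic pattern.** Let correlation be higher within a domain than between domains, from 0.3 within and 0.1 between up to 0.7 and 0.3. By simulation, all 16 give 0.53 down to 0.40, and the 10 give 0.38 down to 0.31. Both lie inside the ranges in Step 3.

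**Step 5: what the count leaves out.** It takes one test per measure at one visit. The article plans assessments at 3 and 6 months, uses both repeated-measures ANOVA (or Friedman) and ANCOVA, and includes instruments with several components. Counting these separately would raise the figures.

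**The case against.** The strongest reply is that ranking secondary outcomes and handling multiplicity among them is commonly left to an analysis plan, which is not shown, and that this is a condensed article. The article promises no familywise control, and reporting labelled secondary outcomes at nominal p-values is a common convention. All of that stands. The missing adjustment is therefore not the point made here. The point is what the article does state: an aim and an abstract conclusion that override its own labels, and one rule for all tests. An unseen plan would not change that wording.

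A reader might infer four stronger things, and the document supports none of them.

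- *That there is no hierarchy.* There is: one primary outcome, one hypothesis and one powered variable. What is lacking is any separation of secondary tests from the primary one in the significance rule and in the aim.
- *That a chance positive is more likely than not.* For the 16 measures that needs nearly independent tests: 0.56 at r = 0, but 0.37 at r = 0.5. For the 10 it is at most 0.40.
- *That the plan breaches a stated 5% familywise rate.* The 0.05 in Statistical considerations is a per-test threshold, and the alpha in Power and sample size belongs to the SPPB.
- *That the Discussion would change practice on any one positive test.* Its sentence is conditional and joins the functional, sedentary, cognitive and emotional domains with *and*. It treats biomarkers as knowledge to be gained, omits quality of life, and is followed by a reference to a single null hypothesis. Read literally, one isolated positive would not satisfy it. The sentence does leave open which measure, or how many, would establish benefit in a domain.

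**Conclusion.** The point holds as a mismatch between the article's labels and its claims. The major aim and the abstract's Discussion give secondary domains, cognition above all, the same standing as the SPPB, and the significance rule does not tell them apart. Under no effect, the chance of at least one p < 0.05 is about 0.21 to 0.56 across the 16 secondary measures and 0.17 to 0.40 across the 10 outside function. In the favourable direction it is 0.10 to 0.33 for the 16. An isolated secondary positive therefore cannot support a domain claim at the nominal 5% level.

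These ranges rest on assumed equal correlations between 0 and 0.8, since the article gives none, and on one test per measure at one visit. The lower ends still exceed the single-test rate about three- to fourfold (0.17 and 0.21 against 0.05; 0.10 against 0.025). The remedy concerns wording and interpretation only.

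**What to change.** Add to Statistical considerations, in substance:

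> The SPPB is the only confirmatory outcome. All other outcomes are secondary and supportive. They will be reported as between-group differences with 95% confidence intervals, and no conclusion of benefit will rest on them alone.

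Reword the major aim in the Objective section and the closing statement of the abstract so that the practice conclusion rests on the SPPB and the other domains are described as supportive. Adjust the main Discussion to match.

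This needs no new participants, data or procedures. Trial status describes a trial still being set up and recruiting, so the change can be made before results are known. The downside is small: an isolated secondary result with p < 0.05 may no longer be presented as a proven benefit.

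If a confirmatory cognitive claim is wanted, one named cognitive measure at one visit could be tested at two-sided 0.05 only when the primary SPPB test is significant. That step, like splitting alpha among the secondary outcomes, is an optional trade-off.

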### Recruitment and randomization

The listing of individuals that meet inclusion criteria will be obtained from the database of Matia and Caser Residential Care Facilities. The primary recruitment strategy will be information provided to the potential participants by the medical and nursing professionals from each nursing home. All the volunteers will receive detailed study information in their reference sites through the research team: objectives, measurement variables and other details about the interventions will be explained orally and in writing, to both potential participants and their families. Informed consent will be obtained from each participant who will sign it after fully understanding the procedures. Afterwards they will be randomly assigned (1:1 ratio) by center through sealed opaque envelopes to either the control or the intervention group by coin-tossing sequence generation.

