### Outcome measures

The primary outcome measure will be the difference in function between intervention and control group assessed by changes in summary ordinal score on the Short Physical Performance Battery [58] (SPPB). SPPB consists of three tests: balance, gait ability and leg strength. The score for each test is given in categorical modality (0–4) based on run time intervals, and the total score will range from 0 (worst) to 12 points (best). The SPPB has been shown to be a valid instrument for screening frailty and predicting disability, institutionalization and mortality. A total score of less than 10 points indicates frailty and a high risk of disability and falls. 1 point change in the total score has demonstrated to be of clinical relevance [59, 60].

The following parameters will be also recorded: age, gender, socioeconomic situation, marital status, Barthel index [51], MEC-35 [52], Lubben Social Network Scale (LSNS-6) [61], Tilburg Frail index [62], Frailty index [63], and Charlson [64] index. Anthropometric data will include body mass index (BMI) and waist-hip ratio; fat mass percentage will be measured using a portable bio-electrical impedance analyzer (Bodystat BIA Quadscan 4000) [65].

Functional examination will include the following (Table 3): Senior Fitness Test [66], instrumented Timed Up and Go test [67] (iTUG; BTS Biomedical G-WALK triaxial accelerometer and gyroscope), comfortable and fast walking speed [68], bilateral handgrip strength test [69] (Jamar dynamometer), Berg balance test [70], static balance and fall-risk by stabilometer [71] (Biodex Balance System SD), as well as active and sedentary periods during everyday life recorded with an accelerometer (Actigraph GT3X model (Actigraph LLC, Pensacola, FL, USA)) that will be worn on the hip with a belt for a 7 day period. The device will be set to quantify the number of steps taken per day. In line with that, active-period intensities will be classified following the criteria developed by Freedson et al. [72] as light, moderate or vigorous intensity and measured in minutes performed in each intensity.

**Table 3 Tab3:** Functional assessment tests

Test (Reference)	Functions/Parameters	Description

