### Power and sample size

Sample size has been calculated to detect minimal significant effects on the variable of physical performance (SPPB) [80, 81]: accepting an alpha risk of 0.05 and a beta risk of 0.20 in a bilateral contrast, 86 individuals are required in order to detect a difference equal to or greater than 1 unit in the SPPB (SD = 2.34). It has been increased the sample size in an additional 20% (loses during follow-up) and 5% (mortality). The resultant sample size is determinate in 114 individuals, therefore 57 individuals per group (intervention and control group).

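### The Discussion reads a non-significant result as exercise failing to hold back decline, without requiring the interval to exclude the 1-point SPPB benefit

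*Protocol article*

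**What the plan says.** The Discussion considers what a negative trial would mean. It states that "failure to reject the null hypothesis would suggest that the progression of the decline associated with the aging process in at-risk persons continues" and ends in disability, whatever benefit physical activity may have. It calls this an important outcome in its own right and adds that it "implies that efforts to hold back the process of disablement in this population should be directed elsewhere". The only trigger for either statement is non-rejection. No estimate, interval or margin is mentioned.

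Elsewhere the article says what benefit would matter. The Objective section sets the hypothesis as a 1-point SPPB improvement, and Outcome measures says that "1 point change in the total score has demonstrated to be of clinical relevance". Power and sample size plans an ordinary two-sided superiority comparison, "accepting an alpha risk of 0.05 and a beta risk of 0.20 in a bilateral contrast", for a difference of 1 unit with SD 2.34. It arrives at 86 individuals before allowance for losses and then: "The resultant sample size is determinate in 114 individuals, therefore 57 individuals per group". Statistical considerations adds an ANCOVA with the baseline measurement as covariate.

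**The concern.** Failing to reject a null of no difference means only that the data are compatible with no difference. It counts against a worthwhile effect only if the interval also excludes one. The article names the worthwhile effect but does not connect it to the conclusion it draws from a null result. In addition, a between-arm test says nothing about whether residents decline: non-rejection is compatible with both arms worsening, holding steady or improving.

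The article expects its results to guide nursing-home practice and policy. A trial that was merely inconclusive could, on the wording given, be reported as a reason to look away from exercise programmes.

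**Working it through.** **Inputs.** SD 2.34, target difference 1 point, two-sided alpha 0.05, power 0.80, 86 individuals before inflation, 114 after, with 20% losses and 5% mortality (all from Power and sample size); 1:1 allocation (Recruitment and randomization). The correlation between baseline and follow-up SPPB is not given, so the values below are assumptions.

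**The plan's own figure.** n per arm = 2 × (1.960 + 0.842)² × 2.34² / 1² = 85.95, so 86 **per arm**, 172 in total. The protocol uses 86 as the total. The inflation step does reproduce approximately: 86 / 0.75 = 114.7, or 86 / 0.8 / 0.95 = 113.2, against 114. Conversely, 114 × 0.75 = 85.5, so about 43 per arm are expected to be evaluable.

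**Precision.** SE = SD × √(2/n); half-width = 1.96 × SE.
- 43 per arm: SE = 2.34 × √(2/43) = 0.505; half-width 0.99 (1.00 with the t quantile).
- 57 per arm, no losses: SE 0.438; half-width 0.86 (0.87 with t).
- ANCOVA, if 2.34 is the raw-score SD: multiply by √(1 − r²). At 43 per arm this gives 0.86, 0.71 and 0.59 for r = 0.5, 0.7 and 0.8.

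**When a null result leaves 1 point open.** A non-significant estimate lies between −h and +h, where h is the half-width. Its interval reaches 1 if the estimate is at least 1 − h. At 43 per arm unadjusted, 1 − 0.99 = 0.01, so practically every non-significant estimate in favour of exercise leaves 1 point inside the interval.

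The share of non-significant results whose 95% interval contains 1 point, from the normal distribution of the estimate, is:

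| Evaluable per arm, analysis | Half-width | True effect 0 | True effect 0.5 | True effect 1 |
|---|---|---|---|---|
| 43, unadjusted | 0.99 | 49% | 80% | 95% |
| 57, unadjusted | 0.86 | 37% | 74% | 93% |
| 43, ANCOVA r = 0.5 | 0.86 | 36% | 74% | 93% |
| 43, ANCOVA r = 0.7 | 0.71 | 19% | 60% | 88% |
| 43, ANCOVA r = 0.8 | 0.59 | 7% | 39% | 72% |
| 57, ANCOVA r = 0.8 | 0.52 | 1% | 9% | 24% |
| 86, unadjusted | 0.70 | 18% | 60% | 87% |

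**When non-significance alone would be enough.** The upper limit of a non-significant result is always below 2h, so non-rejection by itself excludes 1 point only if h is below 0.5. From the unadjusted half-widths, that needs r above √(1 − (0.5/0.989)²) = 0.86 at 43 per arm, or above √(1 − (0.5/0.859)²) = 0.81 at 57 per arm.

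**How often a true 1-point benefit is missed.** Unadjusted: 49% at 43 per arm and 37% at 57 per arm, against the intended 20%, which is what 86 per arm would give.

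**The case against.** Five things can be said for the protocol.

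1. The sentences are hedged Discussion prose. Statistical considerations contains no decision rule, futility margin or conclusion tied to non-significance. A reader might infer that the trial has bound itself to a negative conclusion; the documents do not support that. This stands, and the point concerns interpretation, not the analysis.
2. A half-width of about 1 point is not a fixed property of the trial. The protocol does not say whether 2.34 is the SD of the score or of its change. If it is the score SD, the planned ANCOVA narrows the interval. This also stands, and is why a range is shown.
3. A reader might infer that a null result would usually leave the 1-point benefit open. That depends on the unknown true effect and correlation. Even unadjusted at 43 per arm the share is 49% when the true effect is zero, and with adjustment it can be far lower. Only the weaker statement, that it readily can, is supported.
4. Part of the imprecision comes from a separate defect, the use of the per-arm requirement as the total. This stands and should not be counted twice. But even at 86 per arm a non-significant estimate above about 0.30 would leave 1 point inside the interval.
5. The Discussion contrasts the null with benefits across functional, sedentary-behaviour, cognitive and emotional domains, so it may not mean SPPB alone. The figures here cover SPPB, the only outcome with a stated target. For the others the inference has even less behind it in the text, since no margin is given.

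None of these makes the inference valid, and no other section corrects it.

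**Conclusion.** The stated reading of a non-significant result is wrong as written and should be changed. It takes non-rejection in a superiority comparison as evidence of no worthwhile benefit without asking whether the interval excludes 1 SPPB point. On the protocol's SD and expected evaluable number, with an unadjusted comparison, the two coexist in about half of null results if exercise has no effect and in nearly all if the true benefit is 1 point.

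The logical fault does not depend on those figures. Its frequency does: it rests on the meaning of the SD, on the unreported baseline correlation, on actual losses and on the true effect. Among the scenarios tabulated, none with the planned 114 residents brings the half-width below 0.5, the level at which non-significance alone would suffice.

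**What to change.** In the Discussion, delete the sentence that sends effort to other approaches and replace the reading of non-rejection with wording such as: a non-significant between-arm SPPB difference will be interpreted from its estimate and 95% confidence interval; a clinically relevant benefit will be regarded as ruled out only if the upper limit is below 1 point; otherwise the result will be called inconclusive. The planned ANCOVA can supply the estimate and interval. For outcomes without a stated margin, make no claim of absence of effect from non-significance.

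The cost is wording only; design, data and analyses are unchanged. The sponsor should expect the rule to return an inconclusive verdict fairly often: unadjusted at 43 per arm, it rules out 1 point only if the estimate is below about 0.01. Correcting the sample-size calculation would ease this, but is a separate decision.
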